### Outcomes

2.8

Outcomes, variables, and covariates are listed in Table 2.

Outcomes are pain intensity, current work ability, pain self-efficacy, pain-related fear avoidance beliefs, chronic pain acceptance, depressive symptoms, sleep problems, sickness absence days and number of occupational health care contacts which are collected from OH's medical records.

### Variables

2.9

Pain-related variables

Pain areas, self-perceived risk of current pain becoming persistent is inquired about as well as the use of painkillers, opioid use, and use of chronic-pain medication. Furthermore, non-pharmaceutical pain management tools are also asked about.

Work-ability variables

We measure with questionnaires current ability to do light work for an hour, work ability in the next 3 months, and self-reported sickness-absence days due to any reason and due to pain.

Other variables

Number of days during the prior week spent enjoying life, feeling active, or days feeling tense or restless.

3.0 Covariates

Age, gender, occupational title, height, weight, amount of physical exercise during the past week, what kind of sport, whether the participant has a chronic disease, and if yes, which chronic disease; other medications, whether the participant smokes and how many years has smoked.

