### Participants and recruitment

2.1

The study base comprises the employees of the city of Helsinki, the country's largest employer. The city of Helsinki has its own occupational health services (OHS), which provides OH services for more than 40 000 employees in 800 occupations of 30 industrial fields. The average age of employees in the city of Helsinki in 2014 was 46, the largest age-group in the city being 50–59. The youngest employees were 19 years old and the oldest employees of the city of Helsinki were 65 [37]. We therefore decide to include employees aged 18–65 years. Systematic review stated that most often the exclusion criteria's were psychological conditions, malignancy, recent or scheduled surgery, pregnancy and trauma [38]. Consistently we will exclude severe diseases such as malignancies, which would lead possibly to missed meetings and lost follow-up, and also we exclude a disease such as severe mental illness, which could bias results [39].

Inclusion criteria•18- to 65-year-old Helsinki city employee•Chronic pain (lasting) for 3 months or longer•Suitable for group activity, by being willing to share own thoughts with other group members•Work disability risk being elevated, based on a short screening questionnaire (modified Örebro questionnaire). Screening survey points for work disability ≥50/100

Exclusion criteria•Malignant disease such as cancer or severe mental disease•Participating in another pain-management group•Experiencing a major psychological or physical life crisis•Being at no elevated risk for work disability, Screening survey (modified Örebro questionnaire) points <50/100

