### Sample size calculation

2.2

In this study we have 9 outcomes. In the presence of several outcomes, sample size should be calculated for the outcome with the smallest difference in effect size before and after [40]. Chronic pain patients' pain is usually high, even 7 or higher, and pain often remain with no change in clinical treatment studies. Minimal cut-off change for pain has been detected in previous studies. Salaffi et al., 2004 [41] stated that minimal cut-off point measure of Numeric Rating Scale of NRS pain is −1.0 cm. When pain is 7.5 before intervention, and after intervention 6.5, the effect size is 13%. The difference in pain acceptance and fear-avoidance beliefs may even be larger than 15% pre- and post-intervention [41]. By using stepped wedge analysis on the study design matrix (6 groups with 4 observations of each group) and with 15% detectable minimum difference of the outcome (chronic pain, mean 7.14 in a scale from 0 to 10) we calculated the minimum group sample size to be 10 (when a-error is 0.05 and b-error 0.80) and total number of participants to be 60 [42].

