Sixth meeting:	• Themes of the meeting: new tools to improve pain management, making one's pain management plan • Filling out the follow-up inquiry • Discussion of homework and pain management tools. • Homework: The pain management plan will be given for writing at home
Seventh meeting, 6-month follow-up, Eighth meeting 12-month follow-up for ABC groups	• Themes of the meeting: psychological flexibility, importance of training and awareness skills, work as rehabilitation • Updating the pain management plan

Both participants and interviewers are blinded for the randomization, and at the end of the interview participants are randomized to one of the six groups (A, B, C, D, E, F). In this stepped-wedge design, every participant knows that he or she will receive an intervention, and the researchers know that no one will be left without treatment, which is not the case in conventional RCT [43].

The request for pain-management group activity originates with the patients themselves. Occupational Health Helsinki has provided three other kinds of groups during the previous 5 years (groups for sleep problems, depression, and burnout). The practical framework for our pain-management group is based on the feedback from those groups (size, facilities, timing, length, language, visual tools). After discussion between the leadership of the city of Helsinki and Occupational Health Helsinki, the results of this study will be provided to the participants in the form of the result report (via e-mail) as well as articles in the media (OHC website, Twitter and such).

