### Timetable

2.5

Recruitment lasts for 1 month, with the Screening (Scr) Questionnaire (modified Örebro questionnaire), filled out before the interview and during the interview. ABC groups start their six meetings one month after recruitment ends. The before (Bef)1 questionnaire is completed during the interview and returned at the first meeting. The After (Aft) questionnaire is filled out during the sixth meeting. DEF groups are on the waiting list and get their Bef1 questionnaire by mail, while the first three groups (ABC) are in the intervention. Bef1 is returned in one week. DEF start the intervention, six meetings 4 months after the first intervention. The Bef2 questionnaire is sent by mail to the DEF groups before intervention and collected on the first meeting day. The Aft questionnaire is completed at the end of the sixth meeting, and participants are advised to book time for their own occupational health nurse if a group member wishes support in completing the pain management plan. Aft6m is filled out at the 6-month meeting. The Aft12 m is completed in the meeting 12 months after intervention; the Aft12 m meeting is arranged only for the ABC groups (Fig. 2).

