### Statistical analysis

2.11

The post-intervention period is compared with the pre-intervention (control) period. Linear mixed-effect models allow analysis of repeated measures data and the differences in the outcomes of interest between intervention and control periods. Intention-to-treat analyses are conducted, and time-effect and intra-cluster correlation coefficients reported. When the null hypothesis (i.e., no difference) is rejected, it is always possible to conclude, whatever the results of the study are, that there exists a difference but actually there is not (type-I error or false positive) [51]. Since the sample size is rather small, exact confidence interval for outcomes will be the choice to avoid statistical bias and false-positive or false-negative errors [51].

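### The covariate list leaves out the outcome's own screening value, the only questionnaire measure taken before randomisation in both sequences

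*Protocol article*

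**What the plan says.** Section 3.0 (Covariates) opens with "Age, gender, occupational title, height, weight, amount of physical exercise during the past week, what kind of sport" and goes on to chronic disease, which disease, other medications and smoking. Table 2 has a matching covariate block. It marks kind of sport and named disease as open questions, and other medication, placed among the pain-related variables, is an open question too. Section 2.1 describes an employer with "employees in 800 occupations of 30 industrial fields".

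The screening form is "filled out before the interview and during the interview" (section 2.5), and "at the end of the interview participants are randomized to one of the six groups" (section 2.3). Section 2.5 has the D-F groups receive Bef1 by post during the A-C intervention. In Table 2 the Scr column is marked for pain intensity, depressive symptoms, the 0-10 sleep item and the two fear-avoidance items. It is not marked for work ability, self-efficacy, acceptance or days slept well. Entry requires an Scr sum of at least 50 out of 100 (section 2.1).

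Section 2.11 states: "The post-intervention period is compared with the pre-intervention (control) period". It plans linear mixed models by intention to treat, with the time effect and intra-cluster correlation reported. It names no covariate as a model term.

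**The concern.** In a trial of 60 people, a baseline value of the outcome is usually the most natural covariate. It must be measured before allocation, in the same way in both sequences. Bef1 does not meet that condition: D-F complete it after randomisation, when they are already waiting. Scr does meet it, and it covers pain intensity, the outcome on which the trial is sized. It is absent from the only covariate list in the article.

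That list does contain items with many possible values: a job title and several free-text answers. At stake is precision already paid for and not used, and some loss of precision if the many-valued items were entered uncoded.

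**Working it through.** **The plan's own figure.** Section 2.2: "we calculated the minimum group sample size to be 10 (when a-error is 0.05 and b-error 0.80) and total number of participants to be 60". 6 × 10 = 60, and the target difference is 0.15 × 7.14 = 1.071 points. No standard deviation or intra-cluster correlation is given, so 60 cannot be re-derived. Reading the stated b-error as power and testing two-sided, a plain 30 v 30 comparison gives 60 only if SD = 1.071 / [(1.960 + 0.842) × √(2/30)] = 1.48. The correlation between Scr and later values is not given either. I assume r = 0.3-0.7.

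**Gain from Scr in the planned type of model.** Assumptions: 60 people, 30 per sequence; T = 4 observations (section 2.2 has four per group); period effects; a random person intercept; total variance 1; the same correlation r between any two measurements, Scr included; no further group effect; variances known. Two treatment patterns (A-C / D-F) are tried, because Fig. 1 is not legible here: 0111/0011, which the order of the surveys suggests (Bef1, Aft, Aft6m, Aft12m against Bef1, Bef2, Aft, Aft6m), and 0111/0001.

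The stepped-wedge variance, with the person as unit, is

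Var = I·s²(s² + T·t²) / [A·s² + B·t²], with I = 60, A = I·U − W, B = U² + I·T·U − T·W − I·V,

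where U is the number of treated person-periods, W the sum of squared period totals and V the sum of squared person totals.

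- 0111/0011: U = 150, W = 8100, V = 390, so A = 900 and B = 2700.
- 0111/0001: U = 120, W = 5400, V = 300, so A = 1800 and B = 3600.

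Without Scr, s² = 1 − r and t² = r. Conditioning on Scr removes r² from every variance and covariance, so s² stays at 1 − r and t² becomes r − r² = r(1 − r).

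Example, r = 0.5, 0111/0011: without Scr, 60 × 0.5 × 2.5 / (450 + 1350) = 0.0417, SE 0.204. With Scr, 60 × 0.5 × 1.5 / (450 + 675) = 0.0400, SE 0.200.

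| r | 0111/0011: SE without → with Scr | Reduction | 0111/0001: SE without → with Scr | Reduction |
|---|---|---|---|---|
| 0.3 | 0.235 → 0.232 | 1.3% | 0.185 → 0.179 | 3.0% |
| 0.5 | 0.204 → 0.200 | 2.0% | 0.167 → 0.158 | 5.1% |
| 0.7 | 0.161 → 0.157 | 2.6% | 0.135 → 0.126 | 6.8% |

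The range is about 1-7%. It is small because the repeated measures already supply most of the between-person information that Scr would bring.

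**Occupational title.** If all 800 titles were equally common, 60 people would show 800 × [1 − (1 − 1/800)^60] = 57.8 distinct titles. With concentrated (Zipf) frequencies, exponents 1.0 and 1.2, the expected numbers are 40.9 and 31.4. The range is therefore about 31-58.

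**Cost of fitting raw titles.** Table 2 asks title only before intervention, so it is constant within a person. The worst case is one indicator per person, which leaves the within-person contrast: Var = I·T·s²/B. At r = 0.5 this is 60 × 4 × 0.5 / 2700 = 0.0444 (SE 0.211, 3.3% above 0.204) for 0111/0011, and 120 / 3600 = 0.0333 (SE 0.183, 9.5% above 0.167) for 0111/0001. Over r = 0.7 down to 0.3 the ceilings are 1.6-6.0% and 4.7-17.0%. The effect stays estimable throughout, and fewer distinct titles cost less.

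**The case against.** The strongest reply is that section 3.0 and Table 2 describe data to be collected, not model terms. Section 2.11 fits none of these variables by name, and coding free text and choosing terms is commonly left to an analysis plan. That stands, so the many-valued items are only a secondary point. A repeated-measures model could also take Scr in as an earlier response, and the Fig. 1 legend counts screening among the data-collection points. That is possible, but it would put values selected by the entry cut among the control-period responses. Regression to the mean could then enter the post-versus-pre contrast, to the extent that the time effect does not absorb it.

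A reader might infer three stronger things that the documents do not support.

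- *That the listed covariates cannot be fitted.* The planned model keeps a within-person contrast that survives even one indicator per person. Chronic disease (yes/no) and smoking (three levels) are easily fitted.
- *That Scr is the only covariate that would help.* It exists for four of nine outcomes, and nothing shows that other covariates are useless. The register outcomes have their own six-month pre-intervention counts.
- *That adjustment makes 60 people worth 75-80.* That figure compares covariate adjustment with a change score: variance ratio (1 + r)/2, so 60/0.75 = 80 at r = 0.5 and 60/0.80 = 75 at r = 0.6. No change-score analysis is planned.

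**Conclusion.** The point holds as a modest, costless improvement. The article's covariate list omits the one questionnaire measured before allocation in both sequences, and using it would cut the standard error by about 1-7% for pain intensity, depressive symptoms, the 0-10 sleep item and fear-avoidance. It does nothing for work ability, self-efficacy, acceptance or the two register outcomes. The size rests on assumed correlations of 0.3-0.7, equal across all occasions, on two assumed treatment patterns, and on no extra group effect. Selecting on the Scr sum may lower the correlations and push the gain towards the small end. The secondary point, on many-valued covariates, concerns avoidable loss of precision and not a model that breaks down.

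**What to change.** In sections 3.0 and 2.11, state that for pain intensity, depressive symptoms, the 0-10 sleep item and the two-item fear-avoidance score, the linear mixed model includes the outcome's own Scr value as a fixed covariate, with age and gender. State that Scr enters only as a covariate and never as a control-period response, because entry requires an Scr sum of at least 50. State also that this adjustment does not apply to outcomes without an Scr value.

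Label occupational title, kind of sport, named disease and other medication as descriptive. If any is to enter a model, collapse it to a few levels fixed before the data are seen.

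The cost is wording only; all the data are already collected under the plan.

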### Interpretation and variability of outcomes

2.10

The maximum sum on the Örebro Short Questionnaire is 100. When a sum score is ≥ 50, the result may predict a higher risk for future work disability [45] (Table 2 the Scr test). We compare the before-intervention sum to the after-sum to discover whether work disability has decreased.

Perceived work ability may predict other work-related outcomes such as sickness absence, retirement, and disability [46]. We compare perceived work ability before and after intervention to discover whether our pain management group has any effect on perceived work ability of chronic pain patients. Furthermore, we learn whether returning to work or continuing working with one's normal duties in 3 months improved after intervention.

According to the literature, the pain visual analogical scale (VAS) gives the highest scores for some chronic pain patients before dinner or at bedtime and for other patients before breakfast or at lunch. Those with the greatest pain in the afternoon and at bedtime are more likely to experience widespread pain and difficulty in sleeping as well as making increased use of health services [47]. In other studies, VAS has not been significantly influenced by interventions. Here, we compare VAS before and after intervention to find whether participating in our pain management group reduces VAS.

McCracken defines acceptance of chronic pain as "a pattern of behavior in which activity is pursued in the presence of pain but without the limitations of pain or efforts to avoid or control pain" [48]. We estimate by comparing before and after values whether chronic pain acceptance has improved.

Co-morbidities commonly associated with chronic pain are depression and sleep problems. Depression can reduce acceptance of chronic pain and worsen pain [8] and may worsen chronic pain [10]. We compare before and after value for depression to interpret whether intervention reduces depressive symptoms and sleep problems.

The cognitive-behavioral fear-avoidance model of chronic pain propose that pain-related fear contributes to the development and maintenance of pain-related disability [27]. Fear-avoidance beliefs and behavior are strongly connected to low-back pain and high fear avoidance belief and behavior worsen the prognosis and treatment outcome. Furthermore, health personnel tend to increase chronic pain patients' fear avoidance especially if they themselves have high fear avoidance belief themselves [49]. We compare fear-avoidance beliefs before and after intervention to learn whether our pain management group weakens fear avoidance beliefs.

Self-efficacy beliefs in those with chronic pain may relate to confidence in performing specific tasks or to confidence in coping with pain [50]. We compare self-efficacy before and after intervention and explore whether our pain management group increases self-efficacy.

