Physical symptoms often occur without physical illness; this is called “somatization,” when psychological factors cause a symptom. The somatization tendency makes it more likely that one will seek medical help [34]. Somatization may amplify transient pain sensations, making them more persistent [35]. High self-efficacy attenuates the association between perceived pain and somatization and researchers suggest that clinicians should encourage especially those pain patients' self-efficacy, who are predisposed to somatization [36].

The aim of this study is to examine the effectiveness of pain-management group participation on pain intensity and associated disability, pain self-efficacy, fear-avoidance beliefs, acceptance of chronic pain, and co-occurrent mental or sleep problems in patients with chronic pain as well as their perceived ability to work, their sickness absence (SA) due to pain, and their use of health services.

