### Data collection

2.7

Data collection can be seen in Table 2. Variables. During the recruitment, a short screening questionnaire (Scr), a slightly modified version of the validated Örebro Short Questionnaire is filled out [45]. A question as to the pain lasting more than 3 months is not calculated, it is one of the inclusion criteria. The sum score is calculated based on 10 questions, each earning 0–10 points: pain areas, (head, neck-trapezius, shoulder/upper arm, elbow or lower arm, wrist/hand, upper back, lower back, hip/thigh, knee/shin, ankle/foot-pain), pain intensity, anxiety, depressive symptoms, being able to do light work for an hour, sleep, expected risk of pain remaining persistent, self-perceived ability to work within the next 3 months, two items on fear-avoidance: “I should stop what I am doing until the pain decreases” and “I should not do normal activities or work when I feel pain”. Maximum sum is 100 points.

**Table 2 tbl2:** Variables.

Variables		Questionnaires			
		Scr	Bef1, Bef2	Aft	Aft 6 m, Aft 12 m
*Outcomes*					
	Pain intensity, 1 item (0 = no pain, 10 = the worst possible pain)	x	x	x	x
	Current work ability, 1 item (0 = totally disabled, 10 = the ability to work at its best)		x	x	x
	Pain self-efficacy, 10 items (0 = not at all confident, 6 = completely confident)		x	x	x
	Chronic pain acceptance, 8 items (0 = totally disagree, 6 = totally agree)		x	x	x
	Depressive symptoms, 1 item (0 = not at all, 10 = extremely much)	x	x	x	x
	Sleep problems, I can sleep at night (0 = I can do it despite pain, 10 = I can't do it because of the pain problem)	x	x	x	x
	Sleep problems, days slept well during the past week (0–7)		x	x	x
	Sickness-absence days (6 months before and after intervention)				
	Health care contacts, number of contacts (6 months before and after intervention)				
*Pain-related variables*	Pain areas, 10 areas (0 = no, 1 = yes)	x	x	x	x
	Pain-related fear-avoidance, 2 items (0 = totally disagree, 10 = totally agree)	x	x	x	x
	Fear of movement, 3 items (0 = totally disagree, 6 = totally agree)		x	x	x
	Self-perceived risk of current pain becoming persistent (0 = no risk, 10 = very large) risk)	x	x	x	x
	Use of painkillers during the previous week, 3 items (0 = none, 1 = few times a week, 2 = every day) Anti-inflammatory drug or Paracetamol Strong analgesic, opiate, medications for chronic pain		x	x	x
	Other medication (open question)		x	x	x
	Non-pharmaceutical pain management tools (open question)		x	x	x

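### Section 2.10 reads a fall in the modified Örebro screening sum as a decrease in work disability, although the sum is described as a risk predictor and 80 of its 100 points do not ask about work capacity

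*Protocol article*

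**What the plan says.** Section 2.10 (Interpretation and variability of outcomes) opens with the modified Örebro questionnaire. It notes the maximum of 100 and says that at a sum of 50 or more "the result may predict a higher risk for future work disability". The next sentence gives the planned use of the score after treatment: "We compare the before-intervention sum to the after-sum to discover whether work disability has decreased".

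Section 2.7 (Data collection) defines the sum: "The sum score is calculated based on 10 questions, each earning 0–10 points", and "Maximum sum is 100 points". The items are pain areas, pain intensity, anxiety, depressive symptoms, light work, sleep, expected persistence of pain, work ability over the next 3 months, and two fear-avoidance beliefs. Section 2.7 also says that the same ten questions are repeated in the baseline and follow-up questionnaires.

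Elsewhere the sum serves as a risk screen: section 2.1 admits participants at 50 or more and excludes those below 50. The aim, at the end of the Introduction, includes "pain intensity and associated disability", perceived ability to work and sickness absence. Section 2.8 lists nine outcomes. Current work ability and sickness-absence days are among them; the Örebro sum is not.

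**The concern.** Two adjacent sentences treat the sum as two different things. In the first it is a prognostic score for a state that may come later. In the second, its before-after change is taken to show whether that state has lessened. A change in a predictor is not a change in the thing predicted, least of all when most of the predictor is made of something else.

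Most of this sum is pain, mood, sleep and beliefs. An improvement in those items lowers the sum whether or not anyone is better able to work. Several of them are also reported separately, so one and the same improvement could appear once under its own name and again as reduced work disability. The setting is occupational health and the authors foresee a larger multicentre study based on the results, so a statement that work disability fell would carry weight that this score cannot bear.

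**Working it through.** **Inputs.** Ten items of 0–10 points and the item list (section 2.7); entry cut-off of 50 (section 2.1); list of outcomes (section 2.8).

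**1. The plan's own maximum.** 10 items × 10 points = 100, which agrees with the stated maximum.

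**2. Split of the sum.** Two items ask about capacity for work: "being able to do light work for an hour" and "self-perceived ability to work within the next 3 months".
- Work items: 2 × 10 = 20 points.
- Other items: 8 × 10 = 80 points.

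**3. Overlap with named outcomes.** Pain intensity, depressive symptoms, sleep and the two fear-avoidance items belong to outcomes named in section 2.8: 5 × 10 = 50 points. Table 2 places the two fear-avoidance items under pain-related variables and not under outcomes. On that layout the overlap is 3 × 10 = 30 points.

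**4. How far the other items must fall.** Hold both work items fixed. To go from a baseline sum B to 49, just under the entry cut-off, the mean fall needed on each of the eight other items is (B − 49)/8. One fear-avoidance item mentions work but asks about a belief; if it is counted as a third work item, the split is 30/70 and the divisor is 7.

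| Baseline B | B − 49 | Mean fall, 8 items | Mean fall, 7 items |
|---|---|---|---|
| 50 | 1 | 0.12 | 0.14 |
| 55 | 6 | 0.75 | 0.86 |
| 60 | 11 | 1.38 | 1.57 |
| 70 | 21 | 2.62 | 3.00 |
| 80 | 31 | 3.88 | 4.43 |

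This can happen even with both work items at their worst score throughout: 20 + 30 = 50 becomes 20 + 29 = 49.

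**5. A worked case (hypothetical).** A participant at 56 improves by 2 points on each of pain intensity, anxiety, depressive symptoms, sleep and the two fear-avoidance items. The sum becomes 56 − 6 × 2 = 44, with no change on either work item.

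The value 49 in step 4 is only a convenient yardstick. The argument applies to a fall of any size.

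**Side observation.** Table 2 gives two items for work ability in 3 months, where section 2.7 lists one question. If both entered the sum, there would be 11 items and a maximum of 11 × 10 = 110, which is not the stated 100. The scoring should be reconciled; the point here does not depend on it.

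**The case against.** The strongest reply is that the sentence is loose wording about a score that is not an outcome. It directly follows a statement about risk, and section 2.1 uses the sum as a risk screen, so it may be shorthand for a decrease in work-disability risk. That reading is possible, but it is not what the sentence says, and if it is meant, saying so costs nothing.

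A second reply is that the share of items does not settle what a change in the sum means; that depends on the validation of the cited instrument, which is not at hand. This stands as a limit. The protocol's own account, however, offers prediction of future risk and nothing about tracking present disability.

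Three stronger readings are tempting, and the document does not support them.

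- A reader might infer that the trial has no outcome measuring disability. It does: section 2.8 names current work ability, whose lower anchor in Table 2 is total disability, and sickness-absence days taken from the occupational health records. The paragraph of section 2.10 that follows compares perceived work ability in its own right.
- A reader might infer that the trial's main conclusion would rest on this sum. The sum is not among the nine outcomes, and section 2.2 does not size the trial on it.
- A reader might infer that falling below 50 counts as success. The 50-point cut-off governs entry; the plan states no such criterion for the after-sum.

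Nor can it be said that the course leaves work aside. Table 1 gives the fourth meeting to work and returns to it at follow-up. Work items may well improve, but the sum cannot show whether they did.

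**Conclusion.** The point holds in a limited form. Section 2.10 interprets a change in a risk-screening sum as a change in present work disability. At most 20 of the 100 points concern work capacity (30 if the belief item that mentions work is counted), so the sum can fall with those items unchanged, and that fall would not support the stated conclusion. The finding rests on the item list in section 2.7 and on reading the sentence as written. It makes no prediction about which items will move. It affects the interpretation of this one score and leaves the listed outcomes, the data collection and the rest of the work-ability assessment untouched. It is worth correcting because more direct measures are already in the plan while the explicit claim about work disability is attached to the less direct one.

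**What to change.** In section 2.10:

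1. Describe a before-after change in the sum as a change in the work-disability risk (screening) score.
2. Show the two work items of the sum separately from the other eight.
3. Rest any statement that work disability decreased on current work ability and sickness-absence days, both named outcomes, supported by the light-work item and the 3-month work-ability item.

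The cost is a reworded sentence and one extra table row, with no new data. The downside is that single items are noisier than a ten-item sum, so the statement on work disability may turn out less favourable.
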